## Volunteer Symptom Diary

Volunteers will be asked to keep daily symptom diaries recording oral temperature as well as pain/tenderness, redness, swelling at the injection site and any systemic signs or symptoms for 20 days following each immunization (**Appendix E**). The size of any injection-site reaction will be measured using a standardized clear plastic measurement device (**Appendix F**) and recorded in the volunteer symptom diary.

## Laboratory Testing

Using standard techniques, the clinical laboratory will perform the following tests:

1. Complete blood count plus white blood cell differential
2. Serum creatinine
3. AST
4. ALT
5. Blood type and screen (See Section 6.8.2)
6. HIV assay (FDA-approved screening antibody assay with Western Blot confirmation)
7. HBsAg ELISA
8. HCV (FDA-approved screening antibody assay and immunoblot confirmation or viral PCR confirmation)
9. Urinalysis (in the event of an abnormal urine dipstick test)

Urine -hCG testing will be performed at the clinical trial site using an Food and Drug Administration (FDA)-approved urine pregnancy test kit. Urine dipstick testing will be performed at the trial site using an FDA-approved product.

The anti-Pfs25 and anti-Pvs25 antibody levels and transmission blocking assays for *P. falciparum* will be performed at the MVDB in Rockville, Maryland. The membrane feeding assays for *P. vivax* will be performed at AFRIMS in Thailand. Frozen sera will be shipped from the trial site to the MVDB on dry ice in batches at the discretion of the trial site with consultation from the MVDB. An inventory of each shipment will be maintained by both the trial site and the MVDB.

## Immunologic Testing

### Antibody Assay (ELISA)

Serum antibody levels to the Pfs25 and Pvs25 antigens will be measured by ELISA. Briefly, microwell plates (Dynex Technologies) are coated overnight at 4oC with 100 μL/well of antigen solution (1 μg/mL). Plates are washed with TRIS-buffered saline (TBS) containing 0.1% Tween‑20 (0.1% T-TBS) and blocked with TBS containing 5% skim milk powder for 2 hours at room temperature. After washing with 0.1% T-TBS, serum samples at a dilution of 1:5,000 in 0.5% T-TBS containing 5% skim milk powder are added in triplicate and incubated for 2 hours at room temperature. After incubation, unbound antibodies are removed by washing the plates with 0.1% T-TBS, and 100 μL of alkaline phosphatase-conjugated goat anti-human IgG solution (Kirkegaard & Perry Labs, Gaithersburg, Maryland, 1:1,000 dilution in 0.5% T-TBS containing 5% skim milk powder,) is added to each well and incubated for 2 hours at room temperature. Plates are then washed with 0.1% T-TBS, followed by adding 100 μL of phosphatase solution (Sigma, St. Louis, Missouri) to each well; the plates are then covered with aluminum foil and incubated for 20 minutes at room temperature for color development. The plates are read immediately at 405 nm with a microplate reader (Spectramax 340PC Molecular Devices). The optical density values are used to determine anti-Pfs25 and anti-Pvs25 antibody concentration by comparison to a standard curve generated with known positive control sera included on each ELISA plate.

### Transmission Blocking Assay (Membrane Feeds)

Membrane feeds is an ex vivo assay that measures the ability of vaccine-induced antibodies to block the parasite development in mosquito midgut. In this assay, anopheline mosquitoes (*A. stevensi, A. dirus*) were fed blood meals containing malaria–infected erythrocytes and test antiserum through using a membrane feeder. The mosquitoes are subsequently reared and dissected 7-10 days later to determine the number of oocysts present in the midgut. The percent transmission-blocking can then be calculated as 100*(1-test mosquito infection/control mosquito infection). The *P. falciparum*-infected erythrocytes are obtained from the laboratory *P. falciparum* cultures. *P. vivax*-infected erythrocytes are obtained by collecting venous blood from consenting vivax malaria patients (age > 15) who present to Thai Ministry of Public Health clinics. Volunteers’ blood in the PpPfs25/ISA51 & ScPvs25H/ISA51 malaria vaccine trial will be typed and screened at the screening visit to avoid the potential for red cell agglutination while performing the membrane feeding assay.

## Use, Storage, and Tracking of Specimens and Data

Samples and data collected under this protocol will be used to study malaria and related diseases, and possible adverse reactions to vaccination. No genetic testing will be performed. Access to the specimens will be limited using either a locked room or a locked freezer. Samples and data will be stored using codes assigned by the investigators or their designees. Data will be kept in password-protected computers. Only investigators or their designees will have access to the samples and data.

Specimens will be stored at the MVDB in Rockville, Maryland. Specimens will be tracked using Freezerworks, a software database. After completion of the protocol, specimens will be unlinked and used as references in future studies on malaria and related diseases. The research use of stored, unlinked, or unidentified specimens may be exempt from the need for prospective IRB review and approval. Exemption requests will be submitted in writing to the NIH Office of Human Subjects Research, which is authorized to determine whether a research activity is exempt.

Any loss or unanticipated destruction of specimens (for example, due to freezer malfunction) or data (for example, misplacing a printout of data with identifiers) will be reported to the IRBs. Such a loss will be reported to the NIAID IRB as a protocol violation.

Subjects may decide at any point not to have their specimens stored. In this case, the investigator will destroy all remaining identifiable specimens and report to both the subject and to the IRBs on what was done with the specimens. This decision may not affect the subject’s participation in this protocol or any other protocols.

# Adverse Events Monitoring and Reporting

## Definitions

### Adverse Event (AE)

An AE is any untoward medical occurrence in a trial volunteer administered the experimental vaccine and that does not necessarily have a causal relationship with vaccination. An AE can therefore be any unfavorable and unintended sign (including an abnormal laboratory finding), symptom, or disease temporally associated with the use of the investigational vaccine, whether or not related to it. This includes an exacerbation of pre-existing conditions and intercurrent illnesses. Unchanged pre-existing conditions will not be included as an adverse event. All AEs must be graded for intensity and relationship to the investigational vaccine as described in **Sections 7.2.2** and **7.2.3** in this protocol.

### Serious Adverse Event (SAE)

An SAE is an AE, whether considered related to the investigational vaccine or not, meeting one of the following conditions:

1. Death during the period of protocol-defined surveillance
2. Life threatening: defined as an event that places a subject at immediate risk of death at the time of the event and does not refer to an event that hypothetically might have caused death were it more severe
3. Hospitalization during the period of protocol-defined surveillance: defined as at least an overnight stay in the hospital or emergency ward for treatment that would have been inappropriate if administered in the outpatient setting
4. Results in a congenital anomaly or birth defect
5. Results in a persistent or significant disability or incapacity: defined as a substantial disruption of the study volunteer’s ability to carry out normal life functions
6. Any other important medical event that may not result in death, be life threatening, or require hospitalization, may be considered a serious AE when, based upon appropriate medical judgment, the event may jeopardize the subject and may require medical or surgical intervention to prevent one of the outcomes listed above

## Assessment of Adverse Events

### Identification of AEs

Assessment of safety will include clinical observation and monitoring of hematological, chemical and immunologic parameters. Safety will be evaluated by monitoring of volunteers for local and systemic adverse reactions during the course of the trial. Volunteers will be closely observed in the clinic for 30 minutes following each immunization. Additionally, volunteers will return to the clinic on Days 1, 3, 7, 14, 21, 30 and 60 following each vaccination for clinical assessments. In addition they will return to the clinic 9, 12 and 18 months after the first vaccination. For 20 days after each immunization, volunteers will be asked to keep daily diaries of symptoms, recording oral temperature, as well as a subjective assessment of the extent of induration, erythema, pain/swelling at the site of injection, and any systemic signs and/or symptoms. The size of any injection-site reaction will be measured using a standardized clear plastic measurement device and recorded in the volunteer symptom diary. All AEs will be graded for intensity and relationship to study product as described in **Section 7.2.2 and 7.2.3** in this protocol. A study clinician will be available by telephone or pager 24 hours a day during the study evaluation period. Should a volunteer call a study clinician to report an adverse event, it will be determined at that time if an extra visit(s) will be scheduled, and/or appropriate medical advice will be provided. Additionally, all calls will be documented in the volunteer’s study chart, and discussed with the Principal Investigator.

### Determination of Severity

All AEs will be assessed by the investigator using the following protocol-defined grading system:

Grade 0 (None)

Grade 1 (Mild): No effect on activities of daily living

Grade 2 (Moderate): Partial limitation in activities of daily living (can complete  50% of baseline), or treatment given

Grade 3 (Severe): Activities of daily living limited to < 50% of baseline, or medical evaluation required

Intensity of the following AEs will be assessed by the investigator as described in **Table 3**. All safety laboratory AEs will be graded in severity following the toxicity table in **Appendix G**. Unexpected adverse events not described in the protocol will be graded according to the Cancer Therapy Evaluation Program’s Common Toxicity Criteria, Version 3, National Cancer Institute in **Appendix H**.

| **Table 3: Assessment of Adverse Event Intensity** | | |
| --- | --- | --- |
| **AdverseEvent** | **Grade** | **Intensity** |
| Pain at injection site | 0 | Absent |
|  | 1 | Pain that is easily tolerated |
|  | 2 | Pain that interferes with daily activity |
|  | 3 | Pain that prevents daily activity |
| Erythema at injection site | 0 | 0 mm |
|  | 1 | >0 - <20 mm |
|  | 2 | >20 - <50 mm |
|  | 3 | >50 mm |
| Swelling at injection site | 0 | 0 mm |
|  | 1 | >0 - <20 mm |
|  | 2 | >20 - <50 mm |
|  | 3 | >50 mm |
| Induration at injection site | 0 | 0 mm |
|  | 1 | >0 - <20 mm |
|  | 2 | >20 - <50 mm |
|  | 3 | >50 mm |
| Fever (oral) | 0 | <99.5°F (<37.5°C) |
|  | 1 | >99.5°F - 100.4°F (>37.5°C – 38°C) |
|  | 2 | >100.4°F - 102.2°F (>38°C – 39°C) |
|  | 3 | >102.2°F (>39°C) |
| Headache | 0 | None |
|  | 1 | Headache that is easily tolerated |
|  | 2 | Headache that interferes with daily activity |
|  | 3 | Headache that prevents daily activity |
| Nausea | 0 | None |
|  | 1 | Nausea that is easily tolerated |
|  | 2 | Nausea that interferes with daily activity |
|  | 3 | Nausea that prevents daily activity |
| Malaise | 0 | None |
|  | 1 | Malaise that is easily tolerated |
|  | 2 | Malaise that interferes with daily activity |
|  | 3 | Malaise that prevents daily activity |
| Myalgia | 0 | None |
|  | 1 | Myalgia that is easily tolerated |
|  | 2 | Myalgia that interferes with daily activity |
|  | 3 | Myalgia that prevents daily activity |
| Arthralgia | 0 | None |
|  | 1 | Joint pain that is easily tolerated |
|  | 2 | Joint pain that interferes with daily activity |
|  | 3 | Joint pain that prevents daily activity |
| Urticaria | 0 | None |
|  | 1 | Requiring no medications |
|  | 2 | Requiring PO or topical treatment or IV medication or steroids for <24 hours |
|  | 3 | Requiring IV medication or steroids for >24 hours |

### Association with Receipt of the Study Vaccine

All AEs will have their possible relationship to study vaccine assessed using the following terms:

Definite: Clear-cut temporal association, and no other possible cause.

Probable: Clear-cut temporal association and a potential alternative etiology is not apparent.

Possible: Less clear temporal association; other etiologies also possible.

Remote: Temporal association between the AE and the vaccine or the nature of the event is such that the vaccine is not likely to have had any reasonable association with the observed illness/event (cause and effect relationship improbable but not impossible).

Not Related: The AE is completely independent of vaccine administration; and/or evidence exists that the event is definitely related to another etiology.

The degree of certainty with which an AE can be attributed to administration of the study vaccine will be determined by how well the event can be understood in terms of one or more of the following:

1. The event being temporally related with vaccination or reproduced on re-vaccination.
2. A reaction of similar nature having previously been observed with this type of vaccine and/or formulation.
3. The event having often been reported in the literature for similar types of vaccines.

All local (injection-site) reactions will be considered causally related to vaccination.

## Adverse Event Reporting

All SAEs will be reviewed by a study physician, recorded on the appropriate SAE form, and followed through to resolution by a study physician. All SAEs will be reported by telephone or fax within 1 working day of notification of the SAE occurrence to all of the following:

- IND Sponsor, Regulatory Compliance and Human Subjects Protection Branch Safety Section (RCHSPB Safety)/NIAID: [contact], [contact]; email: [contact].
- Committee on Human Research (Johns Hopkins IRB): [contact], [contact]
- NIAID IRB: [contact], [contact]

Following notification from the investigator, RCHSPB as the IND sponsor, will report events that are both serious and unexpected that are possibly, probably or definitely related to the vaccine, to the FDA within the required timelines: fatal and life-threatening events within 7 calendar days (by phone or fax) and all other SAEs in writing within 15 calendar days. All SAEs not listed as possibly, probably or definitely related will be reported to the FDA at least annually in a summary format and to the IRBs as required by the institution. All local and systemic reactions not meeting the criteria for “serious adverse events” will be captured on the appropriate case report form (CRF). These events will be followed to resolution.

## Adverse Event Monitoring

### Medical Monitor

An independent Medical Monitor has been appointed for oversight of safety in this trial. The Medical Monitor will be available to advise the investigators on trial-related medical questions or problems, and act as a representative for the volunteers’ welfare. Additionally, the Medical Monitor may ask to convene a safety monitoring committee meeting for review of any safety issue or adverse event. The Medical Monitor will review any SAE determined to be possibly, probably, or definitely related to vaccination.

### Safety Monitoring Committee

MVDB, in consultation with RCHSPB, will select three independent monitors to advise RCHSPB and the study investigators on the trial. These individuals will be independent of MVDB and the clinical trial site. The SMC’s primary responsibility will be to monitor volunteer safety. The Principal Investigator is responsible for ensuring that the SMC is aware of all new safety information. The SMC will periodically review individual and cumulative volunteer data on safety and enrollment when making recommendations regarding the safe continuation of the study. If no stopping criteria are met (**Section 7.5**), dose escalation will proceed with approval from the SMC. The SMC will review cumulative safety data for evidence of study-related AEs, adherence to the protocol, and factors that may affect outcome or study data such as protocol violations and losses to follow-up. Because of the staggered start for each dose group, the SMC will meet after the second part of the dose group (n=8) has been evaluated for at least 14 days post-vaccination; such that 35 days of safety data will have accumulated for the first 4 vaccinees, and 21 days of safety data will have accumulated for the remaining 8 vaccinees. The SMC will review the cumulative safety data following the first vaccination of the lower dose group to approve dose escalation, as well as following the second vaccination prior to dose escalation, and whenever the need should arise, to review study conduct and cumulative safety data, as well as at the discretion of the SMC and/or study investigators.

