Seventy two (60 vaccine and 12 placebo) volunteers will be enrolled and assigned to one of six cohorts as outlined in **Tables 1 & 2**. All vaccines will contain the same amount of Montanide® ISA51. As with other recombinant protein vaccines, hypersensitivity reactions would be expected to occur within the first 24 hours after receipt of the vaccine, and other severe local or systemic reactions within 72 hours, and possibly up to 3 weeks post-vaccination. The vaccinations will be staggered within one dose cohort such that four volunteers will be vaccinated three weeks prior to the remaining 8 volunteers. Therefore, 35 days of safety data will be available for the first 4 vaccinees and 21 days of safety data for the remaining 8 volunteers post-vaccination from the lower dose cohort for review by the Safety Monitoring Committee (SMC) prior to dose escalation. Dose escalation will not occur less than 3 weeks from the remaining 8 volunteers in the lower dose cohort being vaccinated. The trial will not proceed to the next dose cohort if, in the clinical judgment of the SMC, the next higher dose would pose an unacceptable safety risk to the volunteers. The PpPfs25 and ScPvs25 formulations will be considered individually by the SMC prior to dose escalation. The following table represents the earliest projected vaccination dates based on the safety intervals described above. These represent only tentative dates and may change based on recommendations of the Safety Monitoring Committee and/or the study staff.

Tables 1 and 2: Vaccination Schedule

| **PpPfs25/ISA51 Vaccine Dose Escalation Schedule** | | | | |  | **ScPvs25/ISA51 Vaccine Dose Escalation Schedule** | | | | |
| --- | --- | --- | --- | --- | --- | --- | --- | --- | --- | --- |
|  |  | Cohort A1: (n=12) | Cohort B1: (n=12) | Cohort C1: (n=12) |  |  |  | Cohort A2: (n=12) | Cohort B2: (n=12) | Cohort C2: (n=12) |
| Date | Week | 5µg | 20µg | 80µg |  | Date | Week | 5µg | 20µg | 80µg |
| 5/23/05 | 0 | **Vax 1 (n=4)** |  |  |  | 6/13/05 |  |  |  |  |
| 5/30/05 | 1 |  |  |  |  | 7/11/05 | 0 | **Vax 1 (n=4** |  |  |
| 6/6/05 | 2 | **Vax 1 (n=5)** |  |  |  | 7/18/05 | 1 |  |  |  |
| 6/13/05 | 3 |  |  |  |  | 7/25/05 | 2 |  |  |  |
| 6/20/05 | 4 | **Vax 1 (n=3)** |  |  |  | 8/1/05 | 3 | **Vax 1 (n=4)** |  |  |
| 8/22/05 |  |  |  |  |  | 8/22/05 |  | **Vax 1 (n=4)** |  |  |
| 9/26/05 | 18 | **Vax 2 (n=4)** |  |  |  | 9/26/05 | 11 |  | **Vax 1 (n=4** |  |
| 10/3/05 | 19 |  |  |  |  | 10/3/05 | 12 |  |  |  |

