| 10/10/05 | 20 |  |  |  |  | 10/10/05 | 13 |  |  |  |
| 10/17/05 | 21 | **Vax 2 (n=5)** |  |  |  | 10/17/05 | 14 |  | **Vax 1 (n=8)** |  |
| 10/24/05 | 22 |  |  |  |  | 10/24/05 | 15 |  |  |  |
| 10/31/05 | 23 |  |  |  |  | 10/31/05 | 16 |  |  |  |
| 11/7/05 | 24 | **Vax 2 (n=3**) |  |  |  | 11/7/05 | 17 | **Vax 2 (n=4)** |  |  |
| 11/14/05 | 25 |  | **Vax 1 (n=4)** |  |  | 11/14/05 | 18 |  |  | **Vax 1 (n=4)** |
| 11/21/05 | 26 |  |  |  |  | 11/21/05 | 19 |  |  |  |
| 11/28/05 | 27 |  |  |  |  | 11/28/05 | 20 | **Vax 2 (n=4)** |  |  |
| 12/5/05 | 28 |  | **Vax 1 (n=8)** |  |  | 12/5/05 | 21 |  |  | **Vax 1 (n=8)** |
| 12/12/05 | 29 |  |  |  |  | 12/12/05 | 22 |  |  |  |
| 12/19/05 | 23 |  |  |  |  | 12/19/05 | 23 | **Vax 2 (n=4)** |  |  |
| 1/23/06 | 28 |  |  |  |  | 1/23/06 | 28 |  | **Vax 2 (n=4)** |  |
| 2/14/06 | 31 |  |  |  |  | 2/14/06 | 31 |  | **Vax 2 (n=8)** |  |
| 3/6/06 | 34 |  |  |  |  | 3/6/06 | 34 |  |  |  |
| 3/13/06 | 35 |  | **Vax 2 (n=4)** |  |  | 3/13/06 | 35 |  |  | **Vax 2 (n=4)** |
| 3/20/06 | 36 |  |  |  |  | 3/20/06 | 36 |  |  |  |
| 3/27/06 | 37 |  |  |  |  | 3/27/06 | 37 |  |  |  |
| 4/3/06 | 38 |  | **Vax 2 (n=8)** |  |  | 4/3/06 | 38 |  |  | **Vax 2 (n=8)** |
| 4/17/06 | 40 |  |  |  |  | 4/17/06 | 40 |  |  |  |
| 4/24/06 | 41 |  |  | **Vax 1 (n=4)** |  | 4/24/06 | 41 |  |  |  |
| 5/15/06 | 44 |  |  | **Vax 1 (n=8)** |  |  |  |  |  |  |
|  |  |  |  |  |  |  |  |  |  |  |
| 8/21/06 | 58 |  |  | **Vax 2 (n=4)** |  |  |  |  |  |  |
| 9/18/06 | 61 |  |  | **Vax 2 (n=8)** |  |  |  |  |  |  |

1. PpPfs25/ISA51 (n=10) or PBS/ISA51 (n=2)

2. ScPvs25/ISA51 (n=10) or PBS/ISA51 (n=2)

* Within each cohort, the volunteers will be staggered such that 4 volunteers (3 volunteers will receive PpPfs25/ISA51 or ScPvs25/ISA51 and 1 will receive placebo) will be vaccinated 3 weeks prior to the remaining 8 volunteers (7 volunteers will receive PpPfs25/ISA51 or ScPvs25/ISA51 and 1 will receive placebo). The lightly shaded area represents the portion of the study that has been completed.

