## Stopping Criteria

If a dose of vaccine is considered unacceptably reactogenic, dose escalation and/or additional vaccinations will be suspended until reviewed by the SMC and IND sponsor (RCHSPB). The communications from the SMC will subsequently be forwarded by the investigators to the NIAID IRB and the clinical trial site IRB. All local adverse events will be routinely reviewed by the SMC prior to granting approval for dose escalation.

The following criteria will be used to define unacceptable reactogenicity of either of the malaria vaccines. PpPfs25H and ScPvs25H will be considered separately:

1. One or more volunteers experience a SAE (as defined in **Section 7.1.2** in this protocol) that is determined to be possibly, probably or definitely related to the vaccine, **OR**
2. One or more volunteers experience hypersensitivity reaction (a Grade 3 or 4 allergic reaction, as defined **Appendix H**) that is probably or definitely related to the vaccine, **OR**
3. Any severe clinical illness occurs that is not explained by a diagnosis that is unrelated to vaccination, **OR**
4. Three or more volunteers in a single dose cohort experience Grade 2 or higher injection site induration or abscess formation requiring drainage for diagnosis and treatment. A volunteer who experiences Grade 2 or higher injection site induration/abscess following the first vaccination, may not receive the final vaccination, **OR**
5. One or more volunteers in a single-dose cohort experience a Grade 3 or higher safety laboratory abnormality (see **Appendix G**), or Grade 3 systemic AE that is determined to be possibly, probably or definitely related to the vaccine, as defined in **Section 7.2.2** in this protocol.

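### The three-week stagger within each cohort has no scheduled review of the first four volunteers before the other eight are vaccinated, and stopping criterion 4 is unlikely to be met by four people

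*Protocol*

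**What the plan says.** Section 3.1 sets the stagger: "The vaccinations will be staggered within one dose cohort such that four volunteers will be vaccinated three weeks prior to the remaining 8 volunteers". The footnote to Tables 1 and 2 gives the make-up of the first group: "4 volunteers (3 volunteers will receive PpPfs25/ISA51 or ScPvs25/ISA51 and 1 will receive placebo) will be vaccinated 3 weeks prior". Section 3.1 also explains the length of the interval. Severe local or systemic reactions are expected within 72 hours and possibly up to three weeks after vaccination.

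On committee review, Section 7.4.2 states that "the SMC will meet after the second part of the dose group (n=8) has been evaluated for at least 14 days post-vaccination". Its purpose follows: "The SMC will review the cumulative safety data following the first vaccination of the lower dose group to approve dose escalation". A further review after the second vaccination is likewise placed before escalation.

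Section 7.5 lists five criteria, and meeting one suspends escalation and/or further vaccination until the SMC and the IND sponsor have looked at it. Two of the single-event criteria open with "One or more volunteers experience a SAE" and "One or more volunteers experience hypersensitivity reaction". Criterion 3 (an unexplained severe illness) and criterion 5 (a Grade 3 laboratory or systemic event) also need only one event. Criterion 4 is the exception: "Three or more volunteers in a single dose cohort experience Grade 2 or higher injection site induration or abscess formation requiring drainage".

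**The concern.** The stagger has the same length as the period in which the protocol expects severe reactions. A reader would therefore expect the data from the first four to inform whether the eight are vaccinated. The protocol uses the interval only to count days of follow-up available for the escalation decision. It names nobody who must look at the first four, and asks for no record that anyone did, before the second part goes ahead.

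This matters most for local reactions, the main expected harm of this adjuvant. Section 1.4.3 reports drained abscesses in an earlier ISA51 trial, and Section 10.3.2 says that severe swelling and/or induration has already been seen with these two vaccines. Local reactions are the one class for which the automatic trigger needs three volunteers. Two drained abscesses among the first three vaccinees would not meet criterion 4. Suspension would then depend on someone judging the events to be SAEs or a severe illness, or choosing to convene the SMC.

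**Working it through.** **1. The plan's own figure.** Section 9.2 gives a probability of 0.80 of seeing at least one event with rate 0.15 in 10 volunteers. The binomial gives 1 − 0.85^10 = 0.803, which agrees. The same model is used below.

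**2. Inputs.**
- First group: 4 volunteers (3 vaccine, 1 PBS/ISA51 placebo). Cohort: 12. Sources: Section 3.1 and the table footnote.
- Criterion 4: at least 3 volunteers in the cohort. Source: Section 7.5.
- Event rate p: the protocol gives no rate for Grade 2 or higher induration or drained abscess with these vaccines, so p is an assumption. Section 1.4.3 supplies three reference values:
  - about 15%, for Grade 2 local reactions of any kind (one investigator's estimate, subcutaneous delivery);
  - 4/20 = 20%, for cold abscess (one unpublished trial, 2 mL given as four injections);
  - 83/187 = 44.4%, for Grade 1 and 2 nodules together, hence an upper bound for the Grade 2 part.
- 50% is added as a scenario.

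**3. Probability that criterion 4 is met in the first four.** If all four ISA51 recipients are at equal risk, P = 4p³(1 − p) + p⁴. If only the three vaccinees can react, P = p³. For the whole cohort, P = P(X ≥ 3) with X ~ Bin(12, p).

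| p | First four, all at risk | First four, vaccinees only | Cohort of 12, all at risk |
|---|---|---|---|
| 0.15 | 0.012 | 0.003 | 0.264 |
| 0.20 | 0.027 | 0.008 | 0.442 |
| 0.444 | 0.233 | 0.087 | 0.954 |
| 0.50 | 0.313 | 0.125 | 0.981 |

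Worked example at p = 0.20: 4 × 0.008 × 0.80 + 0.0016 = 0.0256 + 0.0016 = 0.027.

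For an even chance of being met in the first four, the true rate would have to be 0.61 (all four at risk) or 0.79 (vaccinees only). These figures assume that every event shows within 21 days. The abscesses in Section 1.4.3 appeared two to four weeks after vaccination, so some could come later and the chance within the interval would be lower still.

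**4. Contrast with a one-event trigger.** P(at least one event in four) = 1 − (1 − p)^4, which is 0.478 at p = 0.15 and 0.590 at p = 0.20. A criterion that fires on one event can therefore operate in a group of this size.

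**5. Day counts in Section 7.4.2.** With a 21-day stagger, 14 days for the eight means 21 + 14 = 35 days for the first four, and 21 days for the eight means 21 + 21 = 42. The section gives a meeting at 14 days or more, yet says that 35 and 21 days of data will be in hand. Section 3.1 repeats the pair 35 and 21. Those two figures imply a gap of 35 − 21 = 14 days, not three weeks. Table 1 does show cohort A1 in groups of 4, 5 and 3 at weeks 0, 2 and 4, but part of the schedule is marked as completed.

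**The case against.** The strongest reply is that the first four are not left unwatched.

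- They attend clinic on Days 1, 3, 7, 14 and 21, with safety bloods on Days 3, 7 and 14 (Section 6.5).
- The Principal Investigator must keep the SMC aware of all new safety information, and the SMC can meet whenever the need arises (Section 7.4.2).
- The Medical Monitor may ask to convene it over any adverse event (Section 7.4.1).
- Criteria 1, 2, 3 and 5 are not tied to a scheduled meeting and can suspend vaccination during the gap.
- A drained abscess could be judged an SAE under the last item of Section 7.1.2. Section 7.2.3 counts all local reactions as related, so criterion 1 could then apply.

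All of this stands. A reader might infer that nobody reviews the first four, and the protocol does not support that. The gap is narrower: nothing scheduled or documented is required before the eight are vaccinated.

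A second reply is that criterion 4 is written for the cohort of 12, where it has a 26% chance of being met at a 15% rate and 44% at 20%. A reader might infer that a count of three is wrong. The figures do not show that. They show only that the rule gives little protection at the four-volunteer stage, a use the protocol never claims for it.

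Third, the reference rates come from other routes, volumes and immunogens, whereas this trial gives 0.5 mL intramuscularly. That is fair, and is why a range is shown.

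**Conclusion.** The concern holds in limited form. The protocol specifies a stagger that matches its own risk window, but no scheduled review or release decision on the first four before the other eight are vaccinated. In that interval oversight is discretionary or event-triggered. For induration and drained abscess, the automatic trigger has about a 1% to 3% chance of being met among the first four at assumed rates of 15% to 20%, and 23% to 31% at 44% to 50%. The chance is lower if only vaccinees react. These figures assume independent volunteers, one dose, and rates carried over from other ISA51 trials apart from the 50% scenario.

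By design the second parts hold 6 × 8 = 48 volunteers. It would be tempting to report 48 avoidable exposures, but the protocol does not support that number. Its revision history runs into 2007, the last tentative vaccination date is in September 2006, and part of the schedule is marked as done, so how many remained to be dosed under this version cannot be told.

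Separately, the day counts in Sections 3.1 and 7.4.2 do not fit a three-week stagger.

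**What to change.** Reconcile Sections 3.1, 7.4.2 and 7.5 on three matters.

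1. Give the stagger a stated oversight step. An existing body (the Medical Monitor or the SMC) documents its review of the first four volunteers' safety data before the remaining eight are vaccinated, in any cohort still to be dosed.
2. Have the sponsor and SMC state how criterion 4 is meant to operate while only four volunteers have been vaccinated. No threshold is proposed here.
3. Correct the timing of the SMC meeting so that the days of data quoted for the four and for the eight agree with each other, with the stagger and with the meeting date. The sponsor should say which of these figures is intended.

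The cost is a few sentences of protocol text and a short review per cohort by a body already in place. It needs no new visits or staff. The downside is a possible delay of a few days before the second part of a cohort.
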